## Abstract

**Background:**

About 70% of all mental health disorders appear before the age of 25 years. When untreated, these disorders can become long-standing and impair multiple life domains. When compared with all Canadian youth (of different ages), individuals aged between 15 and 25 years are significantly more likely to experience mental health disorders, substance dependencies, and risks for suicidal ideation and death by suicide. Progress in the treatment of youth, capitalizing on their online responsivity, can strategically address depressive disorders.

**Objective:**

We will conduct a randomized controlled trial to compare online mindfulness-oriented cognitive behavioral therapy (CBT-M) combined with standard psychiatric care versus psychiatric care alone in youth diagnosed with major depressive disorder. We will enroll 168 subjects in the age range of 18 to 30 years; 50% of subjects will be from First Nations (FN) backgrounds, whereas the other 50% will be from all other ethnic backgrounds. There will be equal stratification into 2 intervention groups (INT^1^ and INT^2^) and 2 wait-list control groups (CTL^1^ and CTL^2^) with 42 subjects per group, resulting in an equal number of INT^1^ and CTL^1^ of FN background and INT^2^ and CTL^2^ of non-FN background.

**Methods:**

The inclusion criteria are: (1) age 18 to 30 years, FN background or other ethnicity; (2) Beck Depression Inventory (BDI)-II of at least mild severity (BDI-II score ≥14) and no upper limit; (3) Mini-International Neuropsychiatric Interview (MINI)–confirmed psychiatric diagnosis of major depressive disorder; and (4) fluent in English. All patients are diagnosed by a Centre for Addiction and Mental Health psychiatrist, with diagnoses confirmed using the MINI interview. The exclusion criteria are: (1) individuals receiving weekly structured psychotherapy; (2) individuals who meet the Diagnostic and Statistical Manual of Mental Disorders criteria for severe alcohol/substance use disorder in the past 3 months, or who demonstrate clinically significant suicidal ideation defined as imminent intent, or who have attempted suicide in the past 6 months; and (3) individuals with comorbid diagnoses of borderline personality, schizophrenia, bipolar disorder, and/or obsessive compulsive disorder. All subjects are provided standard psychiatric care defined as 1 monthly session that focuses on appropriate medication, with session durations of 15 to 30 min. Experimental subjects receive an additional intervention consisting of the CBT-M online software program (in collaboration with Nex J Health, Inc). Exposure to and interaction with the online workbooks are combined with navigation-coaching delivered by phone and secure text message interactions.

**Results:**

The outcomes selected, combined with measurement blinding, are key features in assessing whether significant benefits regarding depression and anxiety symptoms occur.

**Conclusions:**

If results confirm the hypothesis that youth can be effectively treated with online CBT-M, effective services may be widely delivered with less geographic restriction.

**International Registered Report Identifier (IRRID):**

PRR1-10.2196/11591

## Introduction

A total of 70% of all mental health problems appear before the age of 25 years. If untreated, these problems can become long-standing disorders that impair multiple life domains [1]. When compared with all Canadian youth (of different ages), the cohort between 15 and 25 years is significantly more likely to experience mental health disorders and substance dependencies and risks for suicidal ideation and death by suicide [2-5]. The current economic costs of mental health are vast, estimated at Can $51 billion annually, with Can $20.7 billion annually due to lost labor force participation [6]. Innovations in internet and smartphone technologies provide opportunities to deliver mental health care in ways that improve outcomes, reduce costs and overcome the geographic barriers that obstruct service equity.

Cognitive behavioral therapy (CBT)—the best-validated psychotherapy [7]—has, in recent years, been integrated with mindfulness meditation (MM), resulting in strong evidence supporting their combined effectiveness [8-14]. Research with this combination, with student populations, by our group, has resulted in psychometric and neurophysiological [9-17] benefits in online single-arm and randomized controlled trials (RCTs). Another online intervention, tested in an RCT, demonstrated significant reductions in glycosylated hemoglobin blood levels in patients with type 2 diabetes [18-20].

Mindfulness interventions gained notice due to the efficacy and low costs of easily learned procedures that fostered attentional skills and present-time awareness ([21-31]; Kirk et al, in press). For over three decades, in-person mindfulness-based stress reduction and acceptance and commitment therapy programs [17-24,32] have reduced mental and physical symptoms, summating in a significant accumulation of evidence supporting their effectiveness in nonclinical [28] and clinically diagnosed populations [29-31]. A recent review of mindfulness-based cognitive behavioral therapy (CBT-M) suggests that internet-based approaches have effects similar to in-person approaches [33] with evidential support from a systematic review of studies published between 2000 and 2018 [33-43]. The reviewed studies (all RCTs) assessed internet-delivered CBT-M programs in terms of changes in anxiety and depression (as primary or secondary outcomes) in adults (mean age ≥18 years) with a clinical diagnosis of depression or anxiety (using the Diagnostic and Statistical Manual [DSM]-IV protocol) [34-43]. In this review of 11 RCTs, a mean Hedges’ g of −0.47 was calculated based on a 45.6% reduction in depression symptoms when compared with the control populations. These reductions are similar to those found in a systematic review reported by Karyotaki et al who calculated a mean Hedges’ g of −0.27 (for depressive symptom reduction) in online, self-guided treatments that solely implemented CBT [44].

Online programs, altogether, can track usage and transmit text or email prompts to motivate adherence, resulting in higher motivation levels [45-48]. Access to a virtual mindfulness-based navigator-coach at greater frequencies than possible with face-to-face communication [45-49], and improved outcomes. The RCT described here combines these features and assesses them with youth with diagnosed major depressive disorders.

## Methods

### Aim

The study aims to evaluate the efficacy of CBT combined with MM to treat youth (aged 18-30 years) diagnosed with major depressive disorder. We will enroll 168 subjects, where 50% of the subjects will be from First Nations (FN) background, while the other 50% will be from all other ethnic backgrounds, stratified in 2 intervention groups and 2 (wait-list) control groups (42 subjects per group, where INT^1^ and CTL^1^ are from FN background and INT^2^ and CTL^2^ are from non-FN background). The intervention groups will be compared with the control groups at baseline, 3 months (mid intervention), and 6 months (post intervention), using validated outcome measures.

### Recruitment and Randomization

Subjects are identified from the wait-lists for services at the Centre for Addiction and Mental Health (CAMH) and through contacts with multiple Toronto-based clinics. Eligible patients interact with a research coordinator who reviews and explains the study. Eligibility is ascertained in person followed by written consent before randomization. The identification of most subjects follows CAMH procedures where research coordinators identify potential participants by prescreening new clinic referrals and notifying the investigative team and the client’s clinician about potential study eligibility. The clinician then asks the client if she/he is willing to meet with a study team member to explore participation. Only when a client agrees, is she/he approached.

A biostatistician at the Department of Biostatistics at University Health Network ([name]) performed an electronic randomization of participants with study IDs to the different groups (INT^1^, INT^2^, CTL^1^, and CTL^2^). The information regarding each study ID with its respective group allocation was transferred onto cards and placed in individually sealed envelopes. After a participant had completed the baseline questionnaires, the research coordinator opened the next envelope in the series to determine participant group allocation and their respective study ID.

On the basis of a careful review of previously successful studies [38,39,41], we determined a sample size of 42 participants per group in 4 groups (total of n=168). Type I error was set at alpha=.05 and power at 80%. Our projected sample size of 168 participants is deemed more than adequate for the detection of small to medium effect size. With an anticipated drop-out rate of up to 20%, we will recruit 208 participants (54 per group).

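### The claim that 168 participants are amply powered for a small-to-medium effect is overstated: the pooled comparison reaches 80% power only towards the medium end of that range

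*Protocol article*

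**What the plan says.** In the Protocol article, Recruitment and Randomization, the sample size rests on earlier trials: "On the basis of a careful review of previously successful studies", "we determined a sample size of 42 participants per group in 4 groups (total of n=168"). The error rates follow: "Type I error was set at alpha=.05 and power at 80" per cent. The conclusion drawn is: "Our projected sample size of 168 participants is deemed more than adequate for the detection of small to medium effect size". No numerical effect, standard deviation, sidedness or target contrast accompanies it.

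The Aim section gives the structure: "42 subjects per group, where INT^1^ and CTL^1^ are from FN background and INT^2^ and CTL^2^ are from non-FN background". It compares the intervention groups with the control groups. Under Primary and Secondary Outcomes, the effect is tested by ANCOVA on change from baseline to 6 months, with the baseline value as covariate.

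The Introduction cites two pooled effects on depression. For internet-delivered CBT-M: "In this review of 11 RCTs, a mean Hedges’ g of −0.47 was calculated". For CBT alone, the other review "calculated a mean Hedges’ g of −0.27 (for depressive symptom reduction) in online, self-guided treatments that solely implemented CBT". Neither is tied to the sample size.

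**The concern.** The adequacy sentence is a positive statement about a property of the design, made next to an 80% power target. It is not a detail left for a later document. If it is taken at face value, a reader of a non-significant result will assume that the trial had a good chance of detecting a modest benefit and will count the result as evidence against one. The article itself cites an effect of 0.27 in related online treatment and describes it as similar to 0.47, so an effect of that size is within what its authors had in view. Whether 168 participants could detect it decides how a null result should be read.

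**Working it through.** **Can 168 be reproduced?** No. The article gives no effect size or standard deviation, so the calculation can only run from the sample size to the detectable difference.

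**Inputs from the article**
- alpha .05, power 80%, 168 = 4 × 42 (Recruitment and Randomization)
- pooled contrast of 2 × 42 = 84 v 84, and 42 v 42 within each stratum (Aim)
- ANCOVA adjusted for baseline (Primary and Secondary Outcomes)
- benchmark effects of 0.47 and 0.27 in absolute value (Introduction)

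**Assumptions**
- The test is two-sided.
- All 168 are analysed, since the drop-out allowance is added on top of 168.
- The baseline-outcome correlation r is 0 (unadjusted), 0.5 or 0.7.
- Small means 0.2 and medium means 0.5, by the usual convention.

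**Detectable difference, unadjusted**

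d = (z for two-sided .05 + z for 80%) × √(2/n) = (1.960 + 0.842) × √(2/n)

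- n = 84 per arm: 2.802 × 0.1543 = 0.432; by the noncentral t, 0.435
- n = 42 per arm: 2.802 × 0.2182 = 0.611; by the noncentral t, 0.619

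**Detectable difference under ANCOVA**

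The residual standard deviation is multiplied by √(1 − r²).

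- r = 0.5: √0.75 = 0.866. Pooled 0.435 × 0.866 = 0.377; one stratum 0.619 × 0.866 = 0.536.
- r = 0.7: √0.51 = 0.714. Pooled 0.435 × 0.714 = 0.311; one stratum 0.619 × 0.714 = 0.442.

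**Power of the pooled comparison, 84 v 84 (noncentral t; d is divided by √(1 − r²) for ANCOVA)**

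| True d | Unadjusted | r = 0.5 | r = 0.7 |
|---|---|---|---|
| 0.20 | 25% | 32% | 44% |
| 0.27 | 41% | 52% | 68% |
| 0.35 | 62% | 74% | 88% |
| 0.47 | 86% | 94% | 99% |
| 0.50 | 90% | 96% | 99% |

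**Correlation needed for 80% power in the pooled comparison**

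r = √(1 − (d/0.435)²)

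- d = 0.35: about 0.59
- d = 0.27: about 0.78
- d = 0.20: about 0.89

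**Unadjusted numbers per arm for 80% power:** 394 at d = 0.20, 217 at 0.27, 130 at 0.35 and 73 at 0.47. The trial has 84.

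**Sidedness.** A one-sided .05 test lowers the unadjusted pooled figure to 0.385, still well above 0.27.

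**The case against.** The strongest defence is that the sentence is loose rather than wrong. It names a verbal range and no number, so there is no calculation to contradict, and a journal article may leave the derivation to a fuller document. On the usual convention, a pooled detectable difference of 0.43 lies inside small to medium. The closer benchmark is also arguably 0.47: it comes from internet CBT-M trials in clinically diagnosed adults, while 0.27 comes from self-guided, CBT-only programmes and this trial adds navigator coaching. At 0.47, pooled power is 86% before any adjustment.

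Much of this stands. It rules out three stronger readings that a reader might infer:

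- *The claim is simply false.* The article fixes no numerical effect, and the design does meet its 80% target in the upper part of the range.
- *The trial detects nothing below 0.43.* That figure ignores the planned baseline adjustment, which lowers it by an amount that depends on a correlation the article does not give.
- *The within-stratum figure of 0.62 contradicts the plan.* The adequacy sentence concerns the total of 168, and the article states no separate hypothesis or power for either stratum.

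The absence of a derivation is likewise not the point here, and the choice of earlier trials cannot be judged without them.

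The defence does not rescue the wording itself. A range that begins at small includes 0.20 and 0.27, and a size cannot be more than adequate there when power is 25% to 68% against an 80% target.

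**Conclusion.** The statement is wrong as written, but moderately so: it is an overstatement that needs rewording, not a failure of the design. For the pooled comparison, 80% power is reached at about 0.43 unadjusted, or 0.38 to 0.31 with ANCOVA if r is 0.5 to 0.7. The larger cited effect is adequately powered. The smaller one is not unless r is about 0.78 or more, and 0.20 would need about 0.89. These figures rest on a two-sided test, 168 analysed participants and assumed correlations. The conclusion about the lower end of the range holds for all the correlations tabulated, while the exact detectable difference does not.

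**What to change.** In Recruitment and Randomization, delete the wording that calls the size more than adequate and the phrase small to medium. Replace the sentence with text such as:

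*With 168 participants analysed (84 intervention v 84 control, FN and non-FN combined), the trial has 80% power at two-sided alpha .05 for a standardized difference of about 0.43 without adjustment, or 0.38 to 0.31 with baseline-adjusted ANCOVA if the baseline-outcome correlation is 0.5 to 0.7 (assumed). Smaller effects, such as 0.27, are not powered at 80% under these assumptions.*

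As a clarification only, because no stratum power is claimed, add:

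*Any comparison within the FN or non-FN stratum (42 v 42) has a detectable difference of about 0.62 unadjusted (0.54 at a correlation of 0.5) and would be reported as an estimate with a 95% CI.*

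The sponsor should confirm sidedness and, if it has data on the correlation, use that value in place of the assumed ones. The cost is one paragraph, with no extra participants and no change to endpoint or analysis. The stated power becomes less favourable.

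### The recruitment target contradicts itself: four groups of 54 make 216, not 208, and the Abstract and Aim give the pre-drop-out figure of 168 as the number to enroll

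*Protocol article*

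**What the plan says.** Recruitment and Randomization sets the base figure: "we determined a sample size of 42 participants per group in 4 groups (total of n=168". The error rates follow: "Type I error was set at alpha=.05 and power at 80" per cent. No numerical effect size is given; the total is only "deemed more than adequate for the detection of small to medium effect size". The section then allows for losses: "With an anticipated drop-out rate of up to 20%, we will recruit 208 participants (54 per group".

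Two other places give a different enrolment figure. The Objective in the Abstract says "We will enroll 168 subjects in the age range of 18 to 30 years", and the Aim says "We will enroll 168 subjects, where 50% of the subjects will be from First Nations (FN) background". Both divide the 168 into two intervention and two control groups of 42, the Abstract ending its description with "2 wait-list control groups (CTL^1^ and CTL^2^) with 42 subjects per group". Neither mentions 208 or a drop-out allowance.

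**The concern.** The sentence that sets the recruitment target holds two numbers that cannot both be right for four equal groups. Elsewhere the verb for 168 is to enroll, although the sample-size paragraph treats 168 as the number wanted before allowing for drop-out.

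A reader therefore cannot tell from the article how many participants are to be randomized, in total or per group. A final report with 168, 208 or 216 participants could each be described as meeting the plan. The wording of the Abstract and Aim matters most, because taken literally it leaves no allowance for drop-out.

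**Working it through.** **Inputs.** From Recruitment and Randomization: four groups, 42 per group, 168 in total, drop-out up to 20%, recruitment of 208, 54 per group. From the Abstract and Aim: 168 to be enrolled, 42 per group.

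**1. The stated pair.**
- 4 × 54 = 216, which is 8 more than 208 (8/208 = 3.8%).
- 208/4 = 52, not 54.

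**2. Can a usual inflation method give both numbers?**
- Dividing by the retained fraction: 168/(1 − 0.20) = 210 in total. Per group, 42/0.80 = 52.5, rounded up to 53, and 4 × 53 = 212.
- Multiplying by 1.20 (a common shortcut): 168 × 1.20 = 201.6, so 202 in total. Per group, 42 × 1.20 = 50.4, rounded up to 51, and 4 × 51 = 204.

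Neither method gives 208 together with 54.

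**3. What each total leaves at 20% loss.** Remaining = N × 0.80; tolerated drop-out = 1 − 168/N.

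| Randomized | Per group | Remaining at 20% loss | Drop-out tolerated before falling below 168 |
|---|---|---|---|
| 168 | 42 | 134.4 | 0% |
| 208 | 52 | 166.4 | 19.2% |
| 212 | 53 | 169.6 | 20.8% |
| 216 | 54 | 172.8 | 22.2% |

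**4. Effect on power.** The article states no numerical effect size and no sidedness, so this step rests on assumptions: a two-sided test at 0.05, both strata pooled into two arms, and an unadjusted two-sample t-test. With 84 per arm (168 in total), the effect detectable at 80% power is d = 0.435. That value serves only as a reference.
- 208 randomized, 83.2 per arm remaining: detectable d = 0.437; power at d = 0.435 is 79.7%.
- 216 randomized, 86.4 per arm remaining: power at d = 0.435 is 81.1%.
- 168 randomized, about 67 per arm remaining: detectable d = 0.488; power at d = 0.435 is 70.5%.

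**5. The same comparison with baseline adjustment.** The analysis section plans ANCOVA with the baseline value as covariate. With baseline–outcome correlation r, the effective standardized effect is d/√(1 − r²). The article gives no r, so a range is shown for d = 0.435.

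| Assumed r | Effective d | Power, 84 per arm | Power, 67 per arm |
|---|---|---|---|
| 0.3 | 0.456 | 84% | 75% |
| 0.4 | 0.475 | 86% | 78% |
| 0.5 | 0.502 | 90% | 82% |

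Losing a fifth of 168 still costs about 8 to 9 percentage points, but from a higher starting level.

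**The case against.** The strongest reply is that this is a slip of the pen with little statistical content. Recruitment and Randomization itself shows how 168 and 208 are related: 168 is the projected sample size and 208 the number recruited to allow for drop-out. The Abstract and Aim simply repeat the first figure with a loose verb. The number 216 is never written; it appears only when 54 is multiplied by four. On this view the Methods contain a sound drop-out allowance, and the rest is copy-editing.

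Much of that stands, and it rules out several stronger readings.
- A reader might infer that 208 is too few. It is short by 1.6 participants against a drop-out figure worded as a ceiling, and the power effect is negligible.
- A reader might infer that 54 per group is also a wrong inflation. It is not: 53 is the minimum, and 54 meets the allowance with a small margin.
- A reader might infer that the trial will lose about 10 points of power. That requires enrolment to stop at 168, which Recruitment and Randomization does not plan. It also uses an effect size that the article never states and sets aside the planned covariate adjustment.
- A reader might infer that the wrong number of envelopes was prepared, or that a stratum will close at the wrong point. The article gives no envelope count and no rule for closing a stratum.

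The reply does not remove the contradiction. No reading makes 208 equal four groups of 54, and nothing in the Abstract or Aim says that 168 means completers. Nor is this a detail left to a fuller document: the article states the figures, and they disagree.

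**Conclusion.** The point holds as a contradiction in a basic design figure. The total and the per-group number in the recruitment sentence differ by 8 participants, and the Abstract and Aim give as enrolment a number that the sample-size paragraph uses before drop-out. These conclusions need only the article's own figures and the four equal groups.

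The statistical consequence of choosing 208, 212 or 216 is small. At the reference effect, power is 79.7% with 208 and 81.1% with 216, with 212 between them. Only literal enrolment of 168 would matter, leaving about 134 at 20% loss. The resulting fall from 80% to about 70% is conditional on an assumed d of 0.435 and an unadjusted two-sided t-test. With an assumed baseline correlation of 0.3 to 0.5, power with 67 per arm would be about 75% to 82%. It should not be presented as an expected loss.

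**What to change.** State one randomization target, with a per-group number that multiplies to it, wherever the figure appears. Any of these is consistent:
- 212 randomized (53 per group), at 20% drop-out;
- 216 randomized (54 per group), at 20% drop-out;
- 208 randomized (52 per group), with the tolerated drop-out restated as 19%.

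In the Abstract and the Aim, replace the statement that 168 will be enrolled with 168 completers (42 per group), and give the randomization target beside it. Check that the allocation list already generated matches the chosen target.

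The cost is a text correction and one check. Relative to 208, choosing 212 adds 4 participants and 216 adds 8; keeping 208 adds none.

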#### Inclusion Criteria

The inclusion criteria are as follows: (1) age 18 to 30 years, FN background or any other ethnicity; (2) Beck Depression Inventory (BDI)-II of at least mild severity but no upper limit (BDI-II score ≥14) [50]; (3) Mini-International Neuropsychiatric Interview (MINI)-confirmed psychiatric diagnosis of major depressive disorder [51]; and (4) fluent in English. All patients are diagnosed by a CAMH physician, and the diagnoses are confirmed using the MINI interview administered at the screening visit [51].

